### Participants

Participants will be recruited from local rehabilitation clinics, fitness centers, and through word-of-mouth referrals. Participants will be eligible to participate if they meet the following criteria:

SCI Group

Diagnosed with traumatic or non-traumatic SCI with ≥4/5 strength in at least one C5 myotome (elbow flexors), enabling the use of an arm ergometer.NLI at or above T6 [21].Classified as A, B, C, or D (motor and sensory complete or incomplete) on the American Spinal Injury Association (ASIA) Impairment Scale (AIS).At least 6 months post-injury and discharged to the community from inpatient rehabilitation prior to enrollment to ensure the stability of vital signs and minimize potential confounding factors associated with acute or subacute phases of SCI [45,46].Aged 18–75 years as HIIE is considered relatively safe within this age range [47].Proficient in English to ensure comprehension of the consent form and cognitive testing.Detectable right middle cerebral artery (MCA) and/or left posterior cerebral artery (PCA) via transcranial Doppler (TCD) [48].

Non-Injured Group

Males or females without a history of SCI.Aged 18–75 years.Proficient in English to ensure comprehension of the consent form and cognitive testing.Detectable right MCA and/or left PCA via TCD.

People showing interest will be screened for medical conditions that preclude exercise instructed by the ACSM’s Guidelines for Exercise Testing and Prescription, such as unstable angina, uncontrolled arrhythmias, recent untreated congestive heart failure, severe valvular disease, and uncontrolled hypertension [49]. Individuals with multiple sclerosis, diabetes, pre-existing shoulder injuries, or those who are pregnant will also be excluded to ensure safety during exercise and to obtain accurate HIIE outcomes on ANS-CV function in the proposed population. Given our focus on ANS-CV outcomes (HR/BP), we will ask participants to abstain from BP medications with direct hemodynamic effects on the day of testing. However, broader medication restrictions will not be mandated but medication names, doses, and purposes will be documented to assess potential medication-related influences on study outcomes.

### Experimental procedure

An initial screening will be conducted remotely through a demographic questionnaire sent via email or conducted over the phone. Interested individuals who meet all eligibility criteria except for detectable right MCA and/or left PCA will be invited for Visit 1. The laboratory ambient temperature will be maintained at 23°C, a thermoneutral range for humans [50]. This will minimize thermal stress risks in SCI participants, who are vulnerable to both hyperthermia and hypothermia due to impaired ANS regulation [4]. Before this visit, they will be instructed to abstain from medications with known effects on BP and HR for at least one-half-life of the medication(s) (with their physicians’ approval), as well as from caffeine, alcohol, and exercise for 24 hours [51]. Additionally, they will be asked to document their dietary intake and maintain their bowel routine. Upon arrival, participants will empty their bladder to limit reflex sympathetic activation. Then, informed consent will be obtained, followed by TCD screening. Two TCD probes will be placed on the temporal area using the transtemporal window to locate the right MCA and/or left PCA [40]. The probes will be secured with a headband, enabling continuous monitoring of CBFV during the trial. A photo of the setup will be taken to facilitate quicker identification of the MCA and PCA during Visit 2. Participants will be included in the study if the right MCA and/or left PCA are detectable. Following this, they will perform a graded exercise test to determine peak power output (PPO), calculated as the product of maximal resistance and the corresponding pedaling rate. Heart rate will be continuously monitored during the test using a Polar HR monitor for safety. Participants will continue to pedal within 25–60 revolutions per minute (rpm) until one of the following criteria are met: (i) volitional exhaustion or (ii) they are unable to maintain 20 rpm during 5 consecutive seconds or (iii) a rating of perceived exertion of 20/20 on the Borg scale [52]. Ratings of perceived exertion (RPE) will be monitored every minute. After the maximal exercise test, two questionnaires on psychological distress and physical activity level will be administrated and a pre-morbid intelligence test using the North American Adult Reading Test will be performed [53].

Visit 2 will be scheduled two to seven days after Visit 1 to allow for recovery from the maximal exercise testing and to ensure that there is no significant change in physical activity levels between the visits. Participants will receive the same pre-visit instructions for both visits, including maintaining a consistent diet, which is important due to its impact on ANS function [54]. Similar to Visit 1, participants will empty their bladder upon arrival to limit reflex sympathetic activation. They will then be seated, and the TCD probes will be secured to measure CBFV. Cognitive function will be evaluated with standard neuropsychological measures including the California Verbal Learning Test-III (CVLT-III) [55], Symbol Digit Modalities Test-oral version (SDMT) [56], Color-Word Interference Stroop Test [57], and the Controlled Oral Word Association Test (COWAT) to assess learning and memory, processing speed, executive function, and verbal fluency, respectively. These domains have been shown to be impacted in people with SCI [58,59]. Following cognitive testing, participants will undergo baseline cardiovascular measurements, including 15 minutes of beat-to-beat BP and electrocardiogram (ECG) recording, followed by a 1-minute face-cooling test (FCT) [60,61] to activate parasympathetic nervous system, a 5-minute recovery and a 15-minute sit-up test (SUT) [62] to activate sympathetic nervous system. To ensure participant safety during these tests and the subsequent HIIE protocol, continuous beat-to-beat BP and ECG monitoring will be conducted. If resting systolic BP exceeds 220 mmHg, the session will be immediately terminated based on a conservative safety threshold, which is well below the established 300 mmHg emergency criterion in SCI [63]. In cases of low BP, continuous monitoring will be maintained, and safety decisions will be guided by symptom presentation, as no universally accepted hypotensive threshold exists for this population.

Participants will then begin with a 2-minute warm-up at 10% PPO, followed by a single bout of HIIE. The HIIE consists of three 20-second all-out efforts at 100% PPO, each separated by 120 seconds of active recovery at 10% PPO. After completing the HIIE, participants will perform a 3-minute cool-down at 10% PPO [64]. This 10-minute protocol is one-third the time commitment of current exercise guidelines for SCI [20], and is therefore feasible for the targeted population. Fig 2 illustrates the HIIE protocol (Fig 2).

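### Participants are told to withhold medication before Visit 1 but consent only on arrival, and the withholding rule is stated in two ways that do not match

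*Protocol article*

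**What the plan says.** Two parts of the protocol article deal with medication before testing.

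- **Participants.** The rule is "we will ask participants to abstain from BP medications with direct hemodynamic effects on the day of testing". The next sentence limits it: "broader medication restrictions will not be mandated but medication names, doses, and purposes will be documented". Physician approval is not mentioned.
- **Experimental procedure, Visit 1.** The first contact is remote: "An initial screening will be conducted remotely through a demographic questionnaire sent via email or conducted over the phone". People who pass it are invited to Visit 1, with this instruction: "Before this visit, they will be instructed to abstain from medications with known effects on BP and HR for at least one-half-life". A parenthesis makes the hold conditional on the physician's approval. After arrival and bladder emptying comes: "Then, informed consent will be obtained, followed by TCD screening".
- **Experimental procedure, Visit 2.** "Participants will receive the same pre-visit instructions for both visits", and "Visit 2 will be scheduled two to seven days after Visit 1".

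Study design also lists consent as a Visit 1 activity. It says that the study is explained to potential participants and that written consent precedes inclusion. No earlier or remote consent is described.

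**The concern.** There are two linked problems.

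**Order.** Asking someone to stop a drug for the sake of a study is a study procedure, so consent should come first. Here the instruction is given before the visit at which consent is taken. The Introduction describes people injured at or above T6 as prone to poor blood pressure and heart rate regulation, including orthostatic hypotension and autonomic dysreflexia, so withholding cardiovascular drugs is not trivial. Some people may also withhold a drug, attend, and then decline consent or fail the transcranial Doppler screen. They would have changed their medication for a study they never enter.

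**Rule.** Two members of staff, each working from a different section, could give the same person different instructions on which drugs to stop and for how long. The medication log would not show which instruction was followed, because time since last dose is not among the items listed for recording.

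**Working it through.** The article gives no figure to reproduce on this point. The check compares the text, with some short arithmetic.

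**1. Sequence under Experimental procedure.** Remote screening, then invitation, then the instruction to withhold, then arrival, bladder emptying, consent, Doppler screening, inclusion if a vessel is detectable, and finally the graded exercise test. The promise in Study design of written consent before inclusion does not cover the hold, because inclusion is decided after the Doppler screen and the hold starts before arrival.

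**2. Count of holds.** For an included person on an affected drug:

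- holds requested = 1 (before Visit 1) + 1 (before Visit 2) = 2
- holds before consent as written = 1 of 2
- holds before consent if consent moves to the remote contact = 0 of 2

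For a person who fails the Doppler screen there is only one hold, and it precedes consent (1 of 1).

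**3. The two rules side by side.**

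| Element | Participants | Experimental procedure |
|---|---|---|
| Drug class | Blood pressure drugs acting directly on hemodynamics | Drugs known to affect blood pressure and heart rate |
| Window | Day of testing | One half-life or longer |
| Physician approval | Not mentioned | Required |
| Wider restriction | Explicitly not mandated | Imposed, for the wider class |

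The drug classes largely overlap. They differ for a drug that affects blood pressure and heart rate but is not a blood pressure drug with direct hemodynamic action.

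**4. Does one window contain the other?** The fraction of drug remaining after time t is 0.5^(t / half-life). The clock times and half-lives below are assumptions for illustration; the article gives none. Take a visit at 10:00.

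- Last dose at 20:00 the evening before, half-life 24 h: t = 14 h. The day-of-testing rule is met. The half-life rule is not, since 14 < 24. Fraction remaining = 0.5^(14/24) ≈ 0.67.
- Last dose at 06:00 the same day, half-life 3 h: t = 4 h. The half-life rule is met, since 4 > 3. The day-of-testing rule is not. Fraction remaining = 0.5^(4/3) ≈ 0.40.

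Neither window implies the other, so the procedural text is not simply a stricter version of the eligibility text.

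**5. Reach into the primary analysis.** Outcome measures lists five primary measures (HF HRV, LF SBPV, BRS, HR, BP), all taken before and after the HIIE bout, which is at Visit 2. So 0 of 5 is collected at Visit 1. Heart rate is observed there, but only for safety: "Heart rate will be continuously monitored during the test using a Polar HR monitor for safety". The pre-consent hold therefore bears on the graded test that sets peak power output, and through it on the exercise load at Visit 2.

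The model under Data analysis tests group by time. If a drug shifts a person's value by d both before and after exercise, then (post + d) − (pre + d) = post − pre, so d adds 0 to that person's change and 0 to the contrast. If the shift differs, d_post − d_pre remains. The article gives neither that difference nor how many people in each group take such a drug, so it cannot be sized.

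**The case against.** The strongest reply has four parts.

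- **A condensed article.** The IRB-approved protocol may describe study information, or even agreement to preparation instructions, at the remote contact. That is possible, and the text does not prove that anyone withheld a drug uninformed. But the article does more than leave the matter open: it states an order, with the hold first and consent second. If practice differs, the article states the order wrongly and still needs correcting.
- **Physician approval.** This is a real safeguard and lowers the clinical risk. It is not the participant's own consent, and only one of the two statements of the rule includes it.
- **The rules can be reconciled.** A participant can satisfy both windows at once, the procedural section is the natural one for staff to follow, and the broader restrictions that are not mandated could mean unrelated drug classes. The first two points are fair and keep the discrepancy modest. The difference in drug class remains, and satisfying both windows is not what either section asks for.
- **No demonstrated effect on results.** This stands. No bias in the group-by-time contrast can be shown from the document, and the count of 1 hold in 2 describes the procedure; it does not estimate harm. The point rests on participant protection and clarity, not on a distorted estimate.

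**Conclusion.** The concern holds on both counts. As written, a study-specific instruction to withhold medication precedes consent, for 1 of the 2 holds asked of an included person on an affected drug. The two statements of the rule differ in drug class, in window and in whether physician approval is needed, and the procedural version is carried forward to Visit 2, where all primary measures are taken.

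This should be corrected, but it is no threat to the primary analysis as far as the document shows. A constant additive drug effect contributes nothing to the group-by-time term, and a non-constant one cannot be sized. The conclusion assumes that the article describes the actual order of events and that no earlier consent is taken. The number of people affected is unknown, so no headcount is given.

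**What to change.** 1. Obtain informed consent before any instruction to withhold medication. The remote screening contact already exists and is the natural place.
2. State one drug class, one window and the physician-approval condition, in identical words in Participants and Experimental procedure. The scope is the investigators' choice; the narrower one in Participants would withhold fewer drugs.
3. Record time since last dose at each visit, next to the drug names, doses and purposes already collected.
4. In the results paper, report which rule the participants already tested had followed.

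Holding drugs only before Visit 2 would also put every hold after consent. It is inferior: peak power output would be set on usual medication and then applied with the drug withheld.

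The cost is an IRB amendment, which the article requires for any protocol change, plus an earlier consent step and one more recorded item. Study status says data collection was under way, with completion expected on May 30, 2025. The first three changes help only people not yet tested; for those already tested, only the reporting step applies.

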Emerging evidence demonstrates that high-intensity-interval exercise (HIIE) offers superior cardiovascular, cerebrovascular and cognitive benefits compared to moderate-intensity continuous training in the general population [31–34]. Additionally, recent work in SCI specifically shows that moderate-to-high intensity arm cycling [12,26,27], but not low-intensity exercise [25], improves ANS-CV function, suggesting that adequate intensity is critical for physiological adaptation in this population. HIIE has emerged as a promising intervention for individuals with SCI, with prior studies demonstrating its feasibility and benefits for cardiorespiratory fitness in this population [35]. The time-efficient nature of HIIE directly addresses a key barrier to physical activity, while its intermittent structure may enhance adherence through greater enjoyment compared to continuous training [35]. While these studies have established the practical advantages of HIIE, its effects on ANS-CV, cerebrovascular, and cognitive functions remain unexplored. It is important to note that ANS dysfunction in people with a NLI at or above T6 might attenuate these benefits, as impaired sympathetic outflow blunts cardiovascular responses during exercise [36,37] and compromises cerebrovascular adaptation [38]. Further, impaired muscle and respiratory function in SCI may reduce physical fitness benefits such as maximal oxygen consumption [21], subsequently limiting hemodynamic and cerebrovascular adaptations to exercise [28]. Therefore, using exercise methods that accommodate preserved motor function in this population, along with inclusion of non-injured controls in studies, will allow direct comparison of HIIE effects in an intact versus ANS compromised cohort to help clarify how SCI influences adaptation to exercise.

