We designed a rigorous prospective case-control study that includes a non-injured control group to bridge the knowledge gap regarding the impact of HIIE on ANS-CV, cerebrovascular, and cognitive functions in individuals with a NLI at or above T6. For this study, we selected arm cycling based on prior evidence of its acute benefits for ANS-CV function in SCI [26]. High-intensity exercise was defined as a rating of perceived exertion (RPE) ≥14 (Borg 6–20 scale) per ACSM guidelines [39]. Although ACSM also classifies intensity using HR (≥70% HR_max_), we prioritized RPE due to ANS dysfunction in SCI at or above T6, which may attenuate HR responses to exercises [36]. The primary aim is to evaluate the effects of a single bout of HIIE on ANS-CV function in individuals with a chronic SCI at or above T6. Secondary aims include assessing the impact of HIIE on cerebrovascular dynamics and cognitive performance in SCI. We hypothesize that an acute HIIE session will improve ANS-CV, cerebrovascular, and cognitive functions in SCI, but these benefits will be attenuated compared to non-injured controls due to ANS dysfunction. To account for individual variability, covariates such as physical activity level, pre-morbid intelligence, and psychological distress will be considered in the analysis.

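### The article states heart rate without a limit as the only physiological safety monitoring for the Visit 1 exhaustive test; its BP and symptom rules are stated for Visit 2 only

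*Protocol article*

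**What the plan says.** **Visit 1 (Experimental procedure).** After consent and transcranial Doppler screening, participants do a graded test that sets peak power output. On safety the text says "Heart rate will be continuously monitored during the test using a Polar HR monitor for safety". Pedalling continues "until one of the following criteria are met: (i) volitional exhaustion or (ii) they are unable to maintain 20 rpm during 5 consecutive seconds". The third end criterion, maximal perceived exertion, is given as "iii) a rating of perceived exertion of 20/20 on the Borg scale". Perceived exertion is recorded every minute. The drug hold reads "Before this visit, they will be instructed to abstain from medications with known effects on BP and HR for at least one-half-life"; physician approval is required for it. Participants are also asked to "maintain their bowel routine", and they empty the bladder on arrival. The room is kept at 23°C.

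**Visit 2 (same section).** Continuous BP and ECG monitoring is stated for the autonomic tests and the interval exercise. A resting systolic BP above 220 mmHg ends the session. Low BP is handled by symptoms. The Sit-up test paragraph under Cardiovascular function lists the hypotension symptoms to ask about.

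**Eligibility (Participants).** Conditions that preclude exercise, including uncontrolled hypertension, are excluded. SCI participants must be at least six months post-injury and living in the community, in part "to ensure the stability of vital signs".

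**Background (Introduction).** In injuries at or above T6, "impaired sympathetic outflow blunts cardiovascular responses during exercise". Orthostatic hypotension and autonomic dysreflexia are named as frequent manifestations. On intensity: "we prioritized RPE due to ANS dysfunction in SCI at or above T6, which may attenuate HR responses to exercises".

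**The concern.** The graded test is the first maximal effort a participant makes in the study. The events the Introduction names for this population, orthostatic hypotension and autonomic dysreflexia, are BP events. The article assigns BP monitoring and BP rules to Visit 2 and states none for Visit 1.

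Eligibility does not supply the missing reading. Initial screening is by e-mailed questionnaire or telephone, and people who meet every criterion except vessel detectability are invited to Visit 1. Uncontrolled hypertension is therefore screened at a distance, and drugs that control BP or heart rate are then held. A high or low pressure on the day would have no stated way of being noticed before the test.

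What is at stake is participant safety. The missing resting BP concerns both groups. The dysreflexia and orthostatic hypotension concern applies to the SCI group.

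**Working it through.** The article gives no figure to reproduce, and the point rests on no power or error-rate calculation. The check sets the stated provisions for the two visits side by side.

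| Provision stated in the text | Visit 1 graded test | Visit 2 tests and interval exercise |
|---|---|---|
| Heart rate or ECG | Polar heart-rate monitor, no limit | Continuous ECG |
| BP reading | None stated | Continuous, beat to beat |
| BP stop | None stated | Resting systolic above 220 mmHg |
| Symptom rule | None stated | Symptom-guided for low BP; symptom questions in the sit-up test |
| Perceived exertion during the graded test | Every minute; 20/20 ends the test | Not applicable |

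**End criteria at Visit 1.** Three are listed. Two rest on the participant's own effort (exhaustion and perceived exertion of 20/20), and one is cadence (under 20 rpm for 5 seconds). 2 + 1 = 3, so the number using heart rate, BP or clinical symptoms is 3 − 3 = 0.

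**Sequence up to the first maximal effort.** Remote screening; drug hold of at least one half-life; bladder emptying; consent; Doppler screening; graded test. No step includes a stated BP reading. The first one stated in the text is at Visit 2, two to seven days later, after the cognitive tests.

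**Other safeguards at Visit 1.** Screening for contraindications, the six-month and community-discharge criteria, physician approval of the drug hold, bladder and bowel preparation, room temperature, exertion ratings and freedom to stop all lower the risk. None is a BP reading. The Doppler probes give flow velocity for vessel detection and measurement, and the article does not describe them as safety monitoring.

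**Reach.** Planned recruitment is up to 20 per group, so at most 2 × 20 = 40 people. The number already tested is not given. A BP check added now reaches between 0 and 40 participants; the SCI-specific symptom criteria reach between 0 and 20.

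**The case against.** The strongest reply is that this is a condensed article. Pre-test BP and in-test safety stops are often left to the full IRB protocol or a laboratory procedure, and a list of end criteria written to define peak power is not a claim that staff would continue through symptoms. Fig 1, the assessment schedule, could not be read for this review, and its legend includes BP. This part stands: a reader might infer that no BP is taken at Visit 1, or that no other safeguard exists, and the documents support neither. What remains is that the article names the Visit 1 safety monitoring and lists the end criteria, and that it spells out BP and symptom rules for the other visit.

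Four further limits are fair.

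- A reader might infer that the protocol itself regards heart rate as an unreliable safety signal. The Introduction discusses attenuated heart rate only as a reason to define intensity by perceived exertion. That the signal may be weak for safety in the SCI group is an inference from that text.
- Participants stay after the test for two questionnaires and a reading test, so they are not sent away at once. That gives contact with staff, though not a stated BP or symptom check.
- The contrast between visits is smaller than it first looks. The 220 mmHg rule is a resting rule, so Visit 2 has no numeric BP stop during exercise either, and the same pre-visit instructions apply to both visits.
- BP before and after the test cannot detect dysreflexia during cranking; only symptoms could. The article's symptom list covers orthostatic hypotension, not dysreflexia.

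**Conclusion.** The point holds as a statement about the article's text. Heart rate without a limit is the only physiological safety monitoring stated for the exhaustive Visit 1 test, 0 of 3 end criteria use heart rate, BP or symptoms, and no in-person BP check is stated before the first maximal effort. The protocol's own account of the population, the remote screening and the drug hold make a check on the day worth having.

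It is a cheap participant-safety improvement. A reader might infer a measurable excess risk, but the documents give no event rate and none can be derived. Endpoints, power and analysis are not affected. The conclusion assumes that neither Fig 1 nor the full IRB protocol already provides these checks. If either does, only the article's wording needs attention.

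**What to change.** At Visit 1:

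1. Take a resting BP in person after consent and before the graded test. Apply the existing resting systolic stop (above 220 mmHg), or a lower limit set by the investigators with the IRB.
2. Repeat BP directly after the test.
3. Add symptoms as reasons to stop the test. For hypotension, reuse the sit-up test list (blurry vision, dizziness, light-headedness, nausea). For dysreflexia, the investigators need to supply a list, because the article has none.

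Leave the uncontrolled-hypertension exclusion as it is. Continuous finger-cuff BP during arm cranking is not requested. If the IRB protocol already contains these checks, a sentence in Experimental procedure settles the point.

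The cost is a few minutes per Visit 1, a short IRB amendment and an occasional stopped session; the laboratory already measures BP. Recruitment began on 14 February 2024, so within this study the change helps only participants not yet tested. It would also serve anyone who reuses the published protocol.
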